**Appendix G Food Cues (CD)**

**Appendix H Cannabis Cues (CD)**

**Appendix G Recruitment Flyers**

**1.0. Background**

**Overview**

Growing evidence linking physical activity to a broad range of desirable health outcomes (e.g., cardio-respiratory health, musculoskeletal health, functional health, energy balance, cancer prevention) indicates the promise of exercise for promoting health and preventing chronic disease. In addition, basic physical activity research in animals and humans has demonstrated the influence of physical activity on the development of cognitive skills, including decision-making, social-emotional learning, executive control processes and attention and much has been learned from animal research about the neurobiological changes induced by exercise regimes. Moreover, intervention research on mood and physical activity indicates significant benefits on mood regulation, stress, and internalizing disorders, especially among depressed adults and children. These areas of research provide a starting point for understanding the role of physical activity across the lifespan in promoting general physical and mental health while simultaneously addressing chronic disease, psychiatric disorder, and substance use. However, few controlled experimental studies have been conducted to examine beneficial effects of exercise on cognition and other health-related behavioral or neurobiological processes and our understanding of the mechanisms that underlie these effects are limited.

This developmental proposal combines expertise from multiple disciplines to bring current knowledge and technological capabilities to the important public health problem of addiction. The overall goal is to explore the relationship between physical activity and addiction. The research team brings experience from addiction ([name]), physical activity ([name]), psychiatric neuroimaging (Drs. [name] and [name]), experimental psychology ([name]), biostatistics ([name]); and neuroimaging physics ([name]). The PI’s laboratory has a primary focus on physical activity and its role in health and disease.

The goal for this project is to obtain pilot data to support R01 application (RFA-DA-09-013; Interactions between Physical Activity and Drug Abuse) (DHHS 2008)for funding for a larger-scale study on interaction between physical activity and functional brain activity in cannabis addiction. Longer-range goals include research designed to improve the translation of existing knowledge of the effects of exercise, physical activity and inactivity into strategies for preventing and treating drug abuse and addiction. Another long-term goal is to research interactions between physical activity and over-eating as contributors to obesity and its health consequences.

**Physical Activity and Addiction**

There are important gaps in the current literature on physical activity and substance use. First, little research has addressed the broad array of substances of abuse; most has focused on tobacco cessation. Second, in the areas of substance use prevention and treatment, the science is not well-developed enough to associate physical activity with reduced risks of substance abuse for non-users and reduced use among those who are diagnosable with a drug use disorder.. Our understanding of how the changes in motivational, emotional, and cognitive processes induced by physical activity have functional significance for drug abuse and addiction is limited. Recent advances in neuroimaging technologies such as fMRI, MRI, PET and evoked response potentials for studying the human brain have the potential to define the effects of physical activity on the brain processes underlying drug abuse behavior and addiction. New animal models are being utilized to study the genetic, molecular, and neurobiological systems that underlie the changes at the cellular level that are triggered by physical activity that have functional consequences for behavior. The results are promising in that these techniques are capable of showing changes in brain structure and function that are related to physical activity. However, further research is needed to better understand the neurobiological and behavioral mechanisms that underlie the link between physical activity and improved psychological well-being.

Many of the brain structures and neural circuits affected by physical activity have also been implicated in the initiation of drugs of abuse, as well as the development of addiction. Given that physical activity has significant effects on some of these same neural networks, exercise may provide a prophylactic effect and/or an ameliorative treatment component in management of drug use disorders. Among the areas of gaps in knowledge are neurobiological and behavioral mechanisms responsible for the effects of physical activity on brain function, drug abuse behavior and addiction across the lifespan as well as research designed to improve the translation of existing knowledge of the effects of exercise and physical activity into strategies for the prevention and treatment of drug abuse.

**Physical Activity and Addiction Treatment**

Exercise has been shown to promote psychological well-being and is sometimes prescribed as an adjunct to treatment for psychiatric disorders such as anxiety and depression. Although recreation therapy is tacitly assumed to be complementary to pharmacological and psychosocial interventions in addiction treatment, relatively little mechanistic research has been conducted to understand the effects of exercise in the treatment of drug dependent individuals. A number of studies have examined the impact of exercise on abstinence rates among nicotine addicted individuals. Some of the findings have been promising, yet more rigorous research is needed that takes into account sample size, acceptability of exercise regimen, follow-up, and other methodological factors. Moreover, the effects of exercise on illicit drug dependence treatment is poorly understood and thus greatly needed.

**Reward System Activated Both by Natural and Drug-Induced Rewards**

Rewarding effects associated with their use provide the initial driving force to take drugs. Numerous studies have described acute effects of different rewarding drugs and the common denominator of their mode of action appears to be release of dopamine in nucleus accumbens.(Di Chiara and Imperato 1988). Similarly, natural behaviors that are essential in daily life and survival of the species also mediate release of dopamine in nucleus accumbens. Also other common behaviors such as playing computer games (Koepp, Gunn et al. 1998), listening to pleasant music (Blood and Zatorre 2001), or watching attractive faces (Aharon, Etcoff et al. 2001) mediate release of dopamine or increase energy consumption in nucleus accumbens. Non-drug associated behaviors can also develop into pathological behaviors such as anorexia nervosa, bulimia nervosa and pathological gambling (see 307.1, 307.51 and 312.31, respectively in Diagnostic and Statistical Manual 4:th edition, (DSM IV)). Similarly, excessive physical training can result in fatigue and mood disturbances as has been reported in overtrained humans (Armstrong and VanHeest). These symptoms are similar to hallmarks of withdrawal in substance abusers, mood disturbances such as depression and anxiety. Also, after withdrawal from an excessive natural rewarding behavior such as running or from addictive drugs the individual will show signs of depression and anxiety or other indications of negative affective states (Koob and Moal 1997). It is not known why long-term use of rewarding drugs can lead from controlled recreational use to out-of-control consumption. Such transition from controlled to compulsive reward seeking behavior is also seen with non-drug induced rewards. With daily repeated administration of the drug this effect gradually increases, a phenomenon termed behavioral sensitization (Wise and Bozarth 1987).

**Cannabis’ Effects on the Brain**

| Brain Region | Functions Associated With Region |
| --- | --- |
| Brain regions in which cannabinoid receptors are abundant | |
| Hippocampus | Learning and memory |
| Cerebellum | Body movement coordination |
| Cerebral cortex, especially cingulate, frontal, and parietal regions | Higher cognitive functions |
| Nucleus Accumbens | Reward |
| Basal ganglia   - Substantia nigra pars reticulata - Entopeduncular nucleus - Globus pallidus - Putamen | Movement Control |
| Brain regions in which cannabinoid receptors are moderately concentrated | |
| Hypothalamus | Body housekeeping functions (body temperature regulation, salt and water balance, reproductive function) |
| Amygdala | Emotional response, fear |
| Spinal cord | Peripheral sensation, including pain |
| Brain stem | Sleep and arousal, temperature regulation, motor control |
| Central gray | Analgesia |
| Nucleus of the solitary tract | Visceral sensation, nausea and vomiting |

**Health Consequences of Cannabis Abuse**

Acute (present during intoxication)

- Impairs short-term memory
- Impairs attention, judgment, and other cognitive functions
- Impairs coordination and balance
- Increases heart rate

Persistent (lasting longer than intoxication, but may not be permanent)

- Impairs memory and learning skills

Long-term (cumulative, potentially permanent effects of chronic abuse)

- Can lead to addiction
- Increases risk of chronic cough, bronchitis, and emphysema
- Increases risk of cancer of the head, neck, and lungs

**Regions of interest**

Exposure to cannabis, both acutely and chronically, is associatedwith changes in brain activity, many paralleling those foundwith other substance use disorders. These findings predominantlyinvolve frontal, limbic and also cerebellar regions, with generallyincreased activity during exposure and generally decreased activityduring abstinence. Findings seen during abstinence may persisteven though they are not necessarily correlated with neuropsychologicaltest results. Regions of differential brain activity appearto involve those implicated with other substance use disordersinvolving the extended dopamine reward pathways, but also apotential frontocerebellar network.

**2.0 Rationale and Specific Aims**

It is unknown how the response of cannabis users might compare to those of non-users in response to similar dose of physical activity. We will therefore compare brain activation during craving to cannabis, a natural reward (food) and a neutral scene (nature images). The food cues will allow us to determine if effects of exercise on brain activation and craving generalize to two different reward conditions and the nature scenes provide a neutral, no rewarding control. In addition to the analysis of predetermined regions of interest, whole-brain exploratory analyses will also be conducted to examine for additional brain regions showing associations between various conditions of interest and regional brain activation.

**Specific Aims**

1. To explore methodological factors involved in finding the relationship between PA and cannabis use.
   1. to examine the effects of cannabis and food cues on brain activation and craving in cannabis users and nonusers
   2. to examine the effects of vigorous exercise on brain activation and craving in response to cannabis and food cues.

Our working hypothesis is that the regional brain activation in response to drug cues will be different in cannabis users than in controls and that exercise will significantly alter brain responses to these cues in both groups. Our secondary hypothesis is that exercise will tend to normalize the abnormal brain activation observed in cannabis users.

Our expectation is that exercise will alter cue-responding in terms of brain activation or craving. It is possible that exercise may be a useful treatment in cannabis dependence. Future studies may examine this specific relationship.

There are no reports available exploring the relationship between physical activity and cannabis use.

Current data suggest that there are convergent findings regardingthe chronic and acute effects of cannabis on brain activity

1. **Inclusion/Exclusion Criteria**

**Inclusion Criteria:**

Cases and Controls must:

- Be able to understand the study and provide written informed consent.
- Be male or female 18 -35 years of age.
- Be right handed
- Be in generally good health based on history, physical examination, electrocardiogram and laboratory findings.
- If female of childbearing potential, have a negative serum pregnancy test on study day

Cases must:

- Meet criteria for cannabis dependence as primary diagnosis as determined by the Substance Abuse module of SCID (Structured Clinical Interview for DSM-IV).
- Not currently seeking treatment for cannabis dependence.
- Have a positive urine drug test for cannabis on the study day
- Avoid alcohol and other recreational drug use (except cannabis and/or nicotine) for 48 h before testing.

**Exclusion Criteria:**

Cases and Controls must not:

- Be pregnant or lactating
- Have implanted electrical medical device (e.g. pacemaker, vagal nerve stimulator)
- Have non-secure metallic foreign bodies
- Have met criteria for another axis 1 diagnosis in the past 6 months
- Receive psychotropically active or vasoactive medications (within 6 weeks of screen day)
- Have chronic medical illness
- Have epilepsy
- Have a history of head injury that required hospitalization
- Have claustrophobia
- Have orthopedic or other problems precluding them from performing exercise protocol
- Have body mass index (BMI) less than 19 kg/m2
- Be heavy smokers (more than 10 cigarettes per day in last 5 years)
- Weighing more than 275 pounds (MRI table limit)

Cases must not:

- Have current dependence, as determined by the SCID, on any psychoactive substance other than nicotine and/or cannabinoid
- Have any serious medical or psychiatric illnesses and/or clinically significant symptoms, which in the judgment of the PI or his/her designee would make them unsafe, or would make compliance with the study protocol difficult or put the study staff at undue risk
- Be under court mandate to obtain treatment

Rationale for inclusion/exclusion criteria:

Participants will include otherwise healthy male and female (18 to 35 years) either cannabis dependence or controls who do not meet criteria for a cannabis abuse or dependence.

Participants in the two groups will be approximately matched by gender, age, height, and educational level. Only right-handed participants will be enrolled to minimize laterality variations in brain function. Overweight volunteers whose weight is greater than 275 pounds (within what we consider a practical safety margin to avoid exceeding the maximum recommended weight for the MRI scanner table of 300 pounds) will be excluded.

All participants will be screened for Axis I psychiatric pathology using a clinical interview conducted by or reviewed with Drs. [name] and [name] to assess for the presence of medical and psychiatric pathology, respectively. Because the presence of an Axis I disorder, as reviewed above, is often co-morbid with cannabis dependence but might confound the interpretation of brain responses, Axis I conditions will be exclusionary for this pilot study.

Screening and study instruments:

- MRI safety screening form
- MINI-structured psychiatric interview (cases only)
- Drug use questionnaire (cases only)
- Nicotine and Caffeine questionnaire
- Marijuana Craving Inventory
- Food Craving Scale

**Screening and study instruments are attached as Appendices A-G.**

1. **Enrollment/Randomization**

Participant recruitment will be conducted using methods previously successful for the recruitment of cannabis users at Vanderbilt. These include flyers and advertisements in local print and audio media outlets, and mass email solicitation. The Vanderbilt Addiction Center will also provide recruitment support services, including listing the study on their Study Finder web site and talking about the study at public meetings. All advertisements will be IRB approved and indicate the research nature of the study. Participants will be screened by phone, and those meeting criteria for enrollment will be scheduled for the study. The study is not blinded (except during data analysis phases, when researchers are blind to exercise condition and group status) and the exercise intervention is randomized.

Written informed consent forms describing the experimental protocols and known risks and hazards, and approved by the Vanderbilt University Medical Center IRB, will be given to participants and the participants will be provided with a copy of the forms. Participants will have the opportunity to ask clarifying questions about the procedure prior to signing the consent forms. The consent will be signed under conditions that give free power of choice without intervention or undue duress, persuasion, coercion, or deception. Consent forms will be stored in a file cabinet in a locked office. Participants will be instructed that they are free to end the study at any time.

**Study Advertisements are attached as Appendix E-F.**  Font size, placement, and bolding will vary. Compensation sentence will not be larger or bolder than other text. Tear-off phone number may be added at bottom of flyers.

**Script for telephone screening is attached as Appendix B.**

**Informed consent form for patients and controls is included in IRB application.**

1. **Study Procedures**

We plan to enroll 35 participants. The study components will consist of an initial phone screen with the participant to verify provisional inclusion criteria. For applicants meeting provisional inclusion criteria, a screening visit will be scheduled for Informed Consent, explanation of study procedures, screening with study instruments and interviews, and an opportunity for a practice session in the mock MRI scanner. For applicants meeting inclusion criteria following screening, a study visit will be scheduled, preferably within 2 weeks of the screening day.

**Table 1. Visit Schedule**

| **Procedure***** | **Visit 1**  **(day 1)** | **Visit 2**  **(day 2-8)** | **Visit 3**  **(days 5-14)** | **Visit 4-12**  **(days 2-10)** |
| --- | --- | --- | --- | --- |
| Consent | X |  |  |  |
| Surveys/questionnaires***** | X | X | X | X |
| Fitness test* | X | X | X |  |
| EKG | X |  |  |  |
| Vital Signs | X |  |  |  |
| Exercise**,*** |  | X | X | X |
| fMRI**** | X | X | X |  |
| Urine Tests | X | X | X | X |
| Buccal cells or Saliva (DNA) | X |  |  |  |
| Breath test | X | X | X |  |

*VO2max – assessment of physical fitness. This test will be done during Visit #1, #2, or #3.

** exercise in randomized order. The participant will be asked to run or jog on a treadmill at a speed approximately 20-50% lower than your fast running speed and/or walk at a comfortable speed during Visit #4 – Visit #12.

*** - Participant may be asked to come to one, two, three, four, five, or six visits.

**** - functional magnetic resonance imaging (test to picture parts of brain). This will be done twice, either during Visit #1 and Visit #3 or during Visit # 2 and Visit #3.

*****On the days a subject is not scheduled for a visit, we may ask questions from the Marijuana Craving Questionnaire, Caffeine and Nicotine Use questionnaire, and Drug use (question Page 13 Question 1: Marijuana (as a dried plant) over the phone. The subject will get copies of these questionnaires so they will know questions we may ask them.

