### Visits 2 and 6.

### Exercise.

### Exercise session will be performed during Visits #4 - #10 at random order.

1. Vigorous exercise.

Each participant will be asked to run/jog on the treadmill for up to 30 minutes at the speed that would be about 20-50% lower than the highest speed they were able to run during the treadmill test at Visit #1 or at a speed that is comfortable to the participant.

During the exercise session, heart rate will be monitored.

1. Light exercise.

Each participant will be asked to walk on the treadmill for 30 minutes at their casual walking speed (2.0 -2.5 METs – metabolic equivalents). During the exercise session, heart rate will be monitored.

**Urine Samples** –Participants will be supplied with urine collection cups and asked to collect a spot urine sample at the beginning of each visit before the exercise session starts.

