**Scans**

Scans will be obtained after 30 minute rest following the exercise. We will conduct neuroimaging sessions at times that are convenient for the participants. The combination of weekday and weekend scan options is chosen to optimize participation of participants who may work or be otherwise occupied during weekdays.

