*Physical: -* Magnetic resonance procedures themselves do not utilize ionizing radiation, and there are no common physical risks to MRI procedures. Minor physical discomfort may occur while lying in the scanner.

*Psychological:* – Potential psychological risks include anxiety during various procedures. Some individuals (5-10%) become claustrophobic in the MR scanner, leading to premature termination of the study. Proposed measures to minimize imaging risks -- The Imaging Institute, including [name] group, has extensive experience in MRI research studies with adults. Our staff and imaging center personnel are very experienced in keeping participants comfortable during scanning procedures. Participants are carefully screened for indwelling metal or medical devices that might pose a danger in the scanner. We follow a complete and in-depth screening procedure designed to identify any participant with a mental health disorder that might make him/her particularly vulnerable to these procedures.

Potential Risk of Exercise Testing (VO2max)

To assess physical capability to perform exercise (walking and running), participant will be given a graded-treadmill test using age appropriate protocol. During the test, participant will be closely monitored and will be instructed to stop the test when they choose. The test will be stopped by the research team if their heart rate exceeds their maximum heart rate (220 – age). The test will be preceded with assessment performed by a physician or designated nurse and would include EKG to screen out participants with abnormal EKG response from the treadmill test.

The criteria include:

- ST-segment depression (defined as ≥1.0 mm of horizontal or down-sloping ST at 80 msec beyond the J point, suggesting myocardial ischemia)
- Ventricular arrhythmias, presenting as frequent multiform PVC, and especially in combination with ST depressions
- Heart rate response that >2 standard deviations (>20 beats/min) below the age-predicted maximal HR who are limited by volitional fatigue
- A change in Diastolic blood pressure >15 mmHg
- Anginal symptoms > 2 (out of 1-4 scale, corresponding to chest pains of perceptible but mild, moderate, moderately severe, and severe intensities, respectively).

Potential Risk of Exercise.

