There is potential risk of injury caused by walking or jogging on the treadmill. The common symptoms include shortness of breath, or more severe, such as falling down. Also, there may be the rare instance of heart problems, such as a heart attack, that could be life threatening. We will do a fitness test to screen if each participant is capable to walk or run for 20 to 30 minutes.

Potential Risks of Genotyping.

There is a very low risk that genotyping information may be disclosed and participant could suffer potential embarrassment or economic harm.

Potential Social/Legal Risks.

There are potential social risks to participants if the confidentiality of the information they provide us is disclosed. For this reason, we follow strict confidentiality procedures.

1. **Reporting of Adverse Events or Unanticipated Problems involving Risk to Participants or Others**

An adverse event (AE) is any untoward medical occurrence in a participant, not necessarily having a causal relationship with the study. A serious adverse event (SAE) is any untoward medical occurrence that a) results in death, b) is life-threatening, c) requires inpatient hospitalization or prolongation of existing hospitalization, d) results in persistent or significant disability/incapacity, or e) is a congenital anomaly/birth defect.

AE’s are graded as:

- Mild (no limitation of usual activities)
- Moderate (some limitation)
- Severe (inability to carry out usual activities)

AE’s are attributed according to the relationship to the study procedures as:

- Not related
- Unlikely
- Possible
- Probable
- Definite

SAE’s are reported immediately by telephone to the VU IRB. Adverse events will be detected by clinical examinations by the studies clinical investigator. An Adverse Event Report form will be completed and returned to the VU IRB within 5 working days. Summary Reports are submitted to the VU IRB and will contain a) The number of adverse events and an explanation of how each event was handled, b) The number of complaints and how each complaint was handled, c) The number of participant withdrawals and an explanation of why the participant withdrew or was withdrawn, and d) The number of protocol violations and how each was handled.

1. **Study Withdrawal/Discontinuation**

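### Table 1 lets the VO2max fitness test fall at Visit 1, 2 or 3, against the exercise section's Visit 1 test, so the test can come after the exercise it is meant to screen for

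*Protocol*

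**What the plan says.** Three parts of the Protocol bear on when the fitness test is done.

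**Schedule (Section 6, Table 1).** The fitness test row is marked at Visits 1, 2 and 3, and the footnote reads "This test will be done during Visit #1, #2, or #3". The EKG row is marked at Visit 1 only. The exercise row is marked at Visits 2, 3 and 4-12. The footnote on exercise has participants run or jog "and/or walk at a comfortable speed during Visit #4" through Visit 12. The day windows are day 1 for Visit 1, days 2-8 for Visit 2, days 5-14 for Visit 3 and days 2-10 for Visits 4-12.

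**Procedures text (Section 6).** VO2max testing is described under the Visit 1 heading, with supine and standing EKGs before it. The exercise text states "Exercise session will be performed during Visits #4 - #10 at random order". It sets the vigorous speed about 20-50% below the "highest speed they were able to run during the treadmill test at Visit #1 or at a speed that is comfortable to the participant".

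**Risks (Section 7).** The purpose of the test is given twice: "To assess physical capability to perform exercise (walking and running), participant will be given a graded-treadmill test", and, after falls and rare heart problems are named as risks of exercise, "We will do a fitness test to screen if each participant is capable to walk or run for 20 to 30 minutes".

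**The concern.** A screening test protects a participant only if its result is known before the exposure. The risks section offers this test as the safeguard against harm on the treadmill, and it lists abnormal exercise responses such as ST-segment depression, ventricular arrhythmia and a low peak heart rate. Table 1 nevertheless lets the test be held at visits whose windows overlap or run past the exercise visits. A participant whom the test would have excluded could already have done run/jog sessions.

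The dose is also affected. The 20-50% rule needs a measured top speed. If the test has not been done, the rule cannot be applied and only the comfortable-speed alternative remains. The vigorous condition is then not tied to a measured maximum for that participant.

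**Working it through.** The plan gives no figure to reproduce. The check sets the places side by side and compares the day windows.

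**1. Which visit is the test visit?**

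| Place in the Protocol | Visit for the test |
| --- | --- |
| Table 1, fitness test marks and footnote | 1, 2 or 3 |
| Section 6, VO2max paragraph | under the Visit 1 heading |
| Table 1, EKG row (EKG precedes the test) | EKG at Visit 1 only |
| Section 6, vigorous exercise | 1 |

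Three places point to Visit 1. Only the fitness test row and its footnote allow a later visit.

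**2. Can exercise at Visits 4-12 precede the test under the day windows?** The exercise days are 2-10, which is 10 - 2 + 1 = 9 days.

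- Test at Visit 1 (day 1): 0 of the 9 exercise days come before it.
- Test at Visit 2 (days 2-8): on any test day from 3 to 8, at least one exercise day comes before it. The longest lag is 8 - 2 = 6 days.
- Test at Visit 3 (days 5-14): on every permitted test day, at least one exercise day comes before it. The longest lag is 14 - 2 = 12 days.
- Visit 3 has 14 - 5 + 1 = 10 permitted days. On 4 of them (days 11-14) the Visit 4-12 window has already closed, so the test follows every such session held in its window.

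**3. Do the exercise marks at Visits 2 and 3 matter?** Yes. If they are followed, a Visit 3 test comes after Visit 2 exercise when those visits run in order. A test held at Visit 2 or 3 also has no stated order against exercise at the same visit.

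**4. Does holding visits in number order remove the problem?** Only if exercise is confined to Visit 4 onward, as the exercise footnote and the exercise text have it, and Visits 4-12 all follow Visit 3. The windows fit that poorly. With Visit 3 on its earliest day (5), days 6-10 remain, which is 5 days for up to nine numbered visits, although another footnote may cap attendance at six visits. With Visit 3 on days 11-14, no Visit 4-12 session can follow it in its window.

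**5. After the change.** With the test at Visit 1 on day 1, all exercise days (2-10) and all of the Visit 2 and Visit 3 windows come later.

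These results show what the text permits. They are not estimates of how often it would happen.

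**The case against.** The strongest reply is that Visit 1 is evidently the intended time and the footnote is the outlier: the procedures text, the EKG row and the speed rule all agree on it. Staff may in practice test everyone at Visit 1. That may be so, but the schedule table is what staff work from, and it says otherwise.

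A second reply is that the safety risk is limited, and this stands in part. Participants are aged 18-35 and in good health on history, examination, EKG and laboratory findings. Those with orthopedic or other problems that preclude the exercise are excluded, and heart rate is monitored during sessions. Without a test, only a comfortable speed is available. A reader might infer that people would exercise unscreened, and the Protocol does not support that. These safeguards still do not do the work of the test, because a heart-rate response limited by volitional fatigue cannot be judged at rest.

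A reader might also infer a bias in the imaging results. The test is allowed at scan visits ("This will be done twice, either during Visit #1 and Visit #3 or during Visit # 2 and Visit #3"), and the only timing rule is "Scans will be obtained after 30 minute rest following the exercise", so a maximal test might shortly precede a scan used for Aim 2. The Protocol does not bear this out as a demonstrated bias. Order within a visit is mostly a detail left unstated. The rest rule can arguably be read to cover an exercise test, though the risks section treats testing and exercise separately. Nothing gives the size or direction of an effect. Table 1 marks no exercise at Visit 1, so the Visit 1 and 3 scan pair does not compare two exercise conditions whenever the test is held.

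**Conclusion.** The point holds as a contradiction in the schedule with a safety consequence, and it should be fixed. Table 1 allows the fitness test at three visits where the rest of the Protocol implies one. At two of those visits the test can follow the exercise it screens for, by up to 6 days (Visit 2) or 12 days (Visit 3). On 4 of the 10 permitted Visit 3 days it follows the entire Visit 4-12 window.

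This assumes that the printed day windows, or the exercise marks at Visits 2 and 3, are followed. If all visits ran in number order and exercise began only at Visit 4, the test would come first. The Protocol does not say that this rule governs, and its windows do not accommodate it when Visit 3 is late. The size of the risk to participants cannot be derived from the document, and the other safeguards moderate it. The order of test and scan is a minor scheduling point.

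**What to change.** Require the fitness test, and review of its result, at Visit 1 before the first exercise session. Remove the Visit 2 and Visit 3 options from the footnote, and remove the fitness test marks in those two columns of Table 1. Where a scan is also done at Visit 1, do the scan before the test.

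This is a wording and schedule amendment with no added procedure. It reduces scheduling flexibility and lengthens Visit 1. Anyone scanned that day would take a maximal test after about 1 hour in the scanner and on top of the 5-hour fast, so the amendment should say how the fast is handled. Some participants scanned at Visit 1 may then be excluded by the test.

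The change gives the 20-50% speed rule a measured anchor. It does not by itself standardise the vigorous dose, because the comfortable-speed alternative remains.
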